
**FIGURE 2 F2:**
[figure not shown]
Spatial layout of fNIRS channels. The figure illustrates the spatial configuration of the fNIRS channels projected onto a standard head model.

#### Participant timeline

Participants will follow a structured timeline throughout the study, consisting of enrollment, intervention sessions, assessments, and follow-up visits.

At the enrollment visit (Week 0), participants will undergo initial screening to confirm eligibility. Baseline assessments will include the MoCA, DST, TMT, MBI, and fNIRS parameters.

During the intervention period (Weeks 1–2), participants will receive 10 sessions of tDCS over 2 weeks, with 5 sessions per week. At the end of Week 2, immediately after the final tDCS session, participants will undergo post-intervention assessments using the same measures as at baseline, including MoCA, DST, TMT, MBI, and fNIRS. For follow-up (Week 14), participants will return 3 months after the last tDCS session for follow-up assessments using the same battery of measures to monitor long-term effects on cognitive function and brain activity. The SPIRIT plan is shown in Table 1.

**TABLE 1 T1:** SPIRIT plan.

	Study period				
Timepoint	Enrolment	Allocation	Post-allocation		Follow-up
		t0	t1	t2	t3
**Enrolment**					
Eligibility screen	√				
Informed consent	√				
Demographic information	√				
Allocation	√	√			
**Interventions**					
Dual-target group			√	√	
Single-target group			√	√	
**Assessments**					
MoCA		√		√	√
Digit span		√		√	√
TMT		√		√	√
MBI		√		√	√
fNIRS		√		√	√

### Sample size

The primary outcome measure for this trial is the MoCA score after 10 treatment sessions. The sample size estimation was conducted using a two-sample means comparison. Based on similar published studies (Gonzalez et al., 2021), it is known that the mean MoCA scores after treatment in the experimental group and the control group are assumed to be 25.7 and 23.7, with standard deviations of 2.4 and 1.7, respectively. With a significance level of α = 0.05 (two-sided test) and a power of 1-β = 0.9, assuming equal sample sizes for the experimental and control groups, the following formula was used:

n=(Z1-α/2+Z1-β)2×(σ12+σ22)δ2

In the formula: Z_1−α/2_ = 1.96, Z_1−β_ = 1.28, σ_1_ and σ_2_ are the pooled standard deviation of the two groups, and δ is the difference between the two group means.

Using the “Two-Sample *T*-Tests Allowing Unequal Variance” option in PASS 2021 software, the calculation determined that each group requires 24 subjects. Considering a dropout rate of 20%, 30 subjects will be enrolled in both the experimental and control groups, totaling 60 subjects, to ensure the scientific rigor of the study design.

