Therefore, a new approach, dual-target anodal tDCS (a-tDCS) has been proposed, demonstrating significant effects in motor performance enhancement. In healthy adults, it significantly enhances corticospinal excitability in the motor cortex, with effects approximately twice as strong as conventional methods and lasting for at least 24 h. This technique may promote long-term brain plasticity by enhancing glutamatergic and NMDA receptor-dependent mechanisms, offering promising applications in motor recovery and neurorehabilitation (Vaseghi et al., 2015). In subacute stroke patients, dual-target a-tDCS improves motor function by reducing reaction time, enhancing hand dexterity, and increasing corticospinal excitability while strengthening connectivity between the DLPFC and primary motor cortex (Achacheluee et al., 2018). In the cognitive domain, dual-target a-tDCS remains underexplored. However, previous studies on dual-target high-definition tDCS (HD-tDCS) provide valuable insights. A recent study showed that dual-target anodal HD-tDCS significantly improved response inhibition in healthy participants (Guo et al., 2022).

Despite its potential, HD-tDCS is complex and costly, posing challenges for widespread application. If a simpler, more affordable method like dual-target a-tDCS can demonstrate similar effectiveness, it could enable broader access to neuromodulation interventions, allowing more patients to benefit from it. This highlights the importance of further investigation into dual-target a-tDCS as a potential alternative in PSCI.

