### Trial design

This study is a single-center, participant-blinded, parallel-group, randomized controlled trial with a 1:1 allocation ratio. The trial is designed as an exploratory study to investigate the effects of dual-target a-tDCS compared to single-target a-tDCS on cognitive functions of patients with PSCI. Participants will be blinded to the intervention they receive, while the operators administering the tDCS will not be blinded due to the nature of the intervention. Outcome assessors and data analysts will remain blinded to group allocation to reduce bias during the evaluation and analysis phases. A detailed overview of the study design and participant flow is illustrated in Figure 1. This study is designed as a comparative trial between two active tDCS conditions (dual-target and single-target). A sham control group is not included due to ethical considerations and the aim to compare different active stimulation protocols rather than to test tDCS efficacy against placebo.

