### Eligibility criteria

#### Inclusion criteria

(1) Confirmed Diagnosis of Stroke: Patients aged 18–80 years with a confirmed diagnosis of ischemic or hemorrhagic stroke, as evidenced by clinical and imaging findings.(2) PSCI: Participants must have a Montreal Cognitive Assessment (MoCA) score less than 26, indicating cognitive impairment following stroke.(3) Time Since Stroke: The stroke must have occurred at least 1 month prior to enrollment, and the patient’s condition should be stable.(4) Language Proficiency: Participants must be native speakers of Chinese with no significant aphasia, enabling them to complete cognitive assessments.(5) Informed Consent: Participants must be willing and able to provide written informed consent to participate in the study.

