### Statistical methods

#### Statistical methods for primary and secondary outcomes

The primary outcome of this study is the change in MoCA scores from baseline to post-intervention and follow-up. The changes in MoCA scores from baseline to post-tDCS intervention, and during the follow-up assessment, will be compared between the experimental and control groups. Homogeneity of variance will be assessed by Levene’s test. For normally distributed continuous data, ANOVA will be used to compare differences between the two groups. If ANOVA indicates significant differences, further post-hoc analysis will be performed using Bonferroni correction. For non-normally distributed continuous data, the Wilcoxon test will be used. The significance level (α) for statistical hypothesis testing will be set at *P* < 0.05. Differences with *P* < 0.05 will be considered statistically significant, while those with *P* > 0.05 will be considered not statistically significant.

Secondary outcomes, including changes in DST, TMT-A and TMT-B, and MBI scores, will be analyzed using similar repeated measures ANOVA methods. For non-normally distributed continuous data, the Wilcoxon signed-rank test will be used for within-group comparisons, and the Mann-Whitney U test will be used for between-group comparisons. fNIRS data will be analyzed using mixed-effects models to assess changes in cortical activation and connectivity, accounting for random effects of participants and fixed effects of group and time. Correlation analysis, such as Pearson correlation coefficient or Spearman correlation coefficient will be conducted to explore the relationships between primary and secondary outcome measures. Lesion location (cortical/subcortical), stroke subtype (ischemic/hemorrhagic), hemispheric lateralization (left/right) and stroke phase (subacute/chronic) will be recorded based on imaging reports. Exploratory analyses may include lesion location and laterality as covariates if appropriate, to explore their influence on intervention outcomes.

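### The 90% power is stated for the raw post-treatment MoCA score, but the planned primary analysis is of change from baseline, for which the plan gives no SD or correlation; the figure is unsupported in either direction.

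*Protocol article*

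**What the plan says.** Two sections of the Protocol article define the primary outcome differently.

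- Sample size: "The primary outcome measure for this trial is the MoCA score after 10 treatment sessions". The calculation is a two-sample comparison of means allowing unequal variances, in which the post-treatment means "are assumed to be 25.7 and 23.7, with standard deviations of 2.4 and 1.7, respectively". It is done "With a significance level of α = 0.05 (two-sided test) and a power of 1-β = 0.9". The result is 24 per group, raised to 30 per group (60 in total) for 20% dropout.
- Statistical methods for primary and secondary outcomes: "The primary outcome of this study is the change in MoCA scores from baseline to post-intervention and follow-up". That section then plans to set the two groups' changes against each other, both at the end of treatment and at follow-up.

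On the population, the Inclusion criteria state: "Participants must have a Montreal Cognitive Assessment (MoCA) score less than 26, indicating cognitive impairment following stroke". No lower limit is set. The low end is restricted only by the requirements on aphasia, ability to complete the cognitive assessments, and written consent.

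The Primary outcomes section reports a MoCA test-retest reliability of 0.96. This is the only figure in the document that bears on the correlation between two MoCA measurements in the same patient, and the sample size calculation does not use it.

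**The concern.** A power figure belongs to a particular variable, test and population. Here the variable in the calculation is a raw score at one time point, while the variable in the analysis is a change at two. Randomisation makes the expected group difference the same for both, so the 2-point difference carries over. The SD does not. The SD of a change depends on r, which the plan does not state.

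The population raises a second question about the same SD. Values of 1.7 and 2.4 around means of 23.7 and 25.7 describe patients clustered near the upper end of the scale. The entry rule would also admit considerably more impaired patients, and the Discussion accepts that mixing subacute and chronic patients may make treatment response more variable.

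At stake is how a null result is read. If the 90% stands without its conditions, a reader may take a non-significant result as good evidence against a 2-point advantage when the design's real sensitivity to that difference is unknown.

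**Working it through.** **Inputs from the Protocol article.** Means 25.7 and 23.7, so δ = 2.0; SDs 2.4 and 1.7; two-sided α = 0.05; power 0.90; 1:1 allocation; 20% dropout (Sample size; Trial design). Test-retest reliability 0.96 (Primary outcomes).

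**Assumed, because the document gives no value.** r from 0.3 to 0.9; a common raw SD of 3 or 4 at both visits as alternatives to the planning SDs.

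**1. Reproduce the stated size.** The printed formula gives n = (1.96 + 1.28)² × (2.4² + 1.7²) / 2.0² = 10.4976 × 8.65 / 4 = 22.70, so 23. The Welch test with the noncentral t distribution gives 88.9% power at n = 23 and 90.2% at n = 24, so 24 is right for the software option named. Then 24 / 0.8 = 30 per group. There is no arithmetic error.

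**2. What the planning SDs imply about the patients.** Under normality, 95% of controls lie in 23.7 ± 1.96 × 1.7 = 20.4 to 27.0. The experimental range is 25.7 ± 1.96 × 2.4 = 21.0 to 30.4, slightly past the scale maximum of 30. The root-mean-square SD is √(8.65 / 2) = 2.08. For illustration only, whole-number scores spread evenly over 15–25 have SD 3.2, and over 10–25 SD 4.6.

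**3. SD of change.** With equal SDs at the two visits, SD(change) = SD × √(2(1 − r)). This equals the raw SD at r = 0.5, is larger below that and smaller above it.

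**4. Power for the change score and detectable difference** (δ = 2 for power; 24 analysed per group; Welch test):

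| Raw SD | r | SD of change | Power | Difference detectable with 90% power |
|---|---|---|---|---|
| 2.4 / 1.7 (plan) | 0.3 | 2.84 / 2.01 | 79% | 2.4 |
| 2.4 / 1.7 (plan) | 0.5 | 2.40 / 1.70 | 90% | 2.0 |
| 2.4 / 1.7 (plan) | 0.7 | 1.86 / 1.32 | 99% | 1.5 |
| 3 (assumed) | 0.5 | 3.00 | 62% | 2.9 |
| 3 (assumed) | 0.7 | 2.32 | 83% | 2.2 |
| 3 (assumed) | 0.9 | 1.34 | 99.9% | 1.3 |
| 4 (assumed) | 0.5 | 4.00 | 40% | 3.8 |
| 4 (assumed) | 0.7 | 3.10 | 59% | 3.0 |
| 4 (assumed) | 0.9 | 1.79 | 97% | 1.7 |

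**5. Break-even.** With equal SDs, 90% power needs an SD of the analysed variable of about 2.09. Solving 2.09 = SD × √(2(1 − r)) gives r ≈ 0.76 at raw SD 3 and r ≈ 0.86 at raw SD 4. At the planning SDs the break-even is r ≈ 0.5.

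**6. If r equalled the quoted 0.96.** The SD of change at raw SD 4 would be 4 × √0.08 = 1.13, and power would be close to 100%.

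**The case against.** The strongest reply is that the mismatch may help the trial. Stable differences between patients cancel in a change score. A wide entry range inflates the raw SD but also tends to raise r, so the two should not be varied as if unrelated. At the planning SDs any r above about 0.5 gives at least the stated power, and the only correlation in the document is 0.96. All of this stands, and it rules out calling the trial underpowered. It does not rescue the 90%: test-retest reliability is an upper guide to r, because uneven recovery and uneven response to treatment both lower the baseline-to-post correlation, and the calculation rests on no value of r.

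The entry rule should also not be read as admitting every score from 0 to 25. Consent capacity, absence of significant aphasia and ability to complete the assessments all trim the low end. The document gives no SD for the resulting population.

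A reader might further infer that a post-treatment mean of 25.7 is implausibly near the entry limit, or that the 2-point difference is too large. The first is attributed to a published study that is not at hand, and 25.7 still lies below 26. On the second, the Background says "In the cognitive domain, dual-target a-tDCS remains underexplored", but that does not contradict planning from similar studies, and the rationale for the comparator says that single-target effects in this condition are limited as well as that the method works elsewhere. Neither inference is supported.

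Finally, the plan calls itself exploratory and lists its small sample as a limitation. That softens the consequence but leaves two conflicting definitions of the primary outcome.

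**Conclusion.** The point holds as an inconsistency and a missing justification. The sample size is correct for the raw post-treatment score at SDs of 2.4 and 1.7. The primary outcome in the analysis section is a different variable, and nothing in the document supplies its variability in the patients the entry rule admits. The 90% is therefore unsupported for the planned analysis.

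A reader might conclude from the lower rows of the table that the trial is underpowered, or that a restated power would probably be worse. The document does not support that. Over the values shown, power for a 2-point difference runs from 40% to nearly 100%, and a high r would put it above 90%. The range rests on assumed raw SDs of 3 and 4, assumed r, equal SDs at the two visits, normality and 24 analysed per group. The existence of the mismatch needs none of these assumptions.

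**What to change.** Keep n = 60 and make these changes.

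1. Let the Sample size and Statistical methods sections name the same single primary endpoint and time point. A suitable choice is MoCA at the end of Week 2, compared between groups with baseline MoCA as a covariate; the follow-up comparison is then secondary.
2. State that the 90% is conditional on SDs of 2.4 and 1.7 for the post-treatment score.
3. For the analysis adopted, give power and the detectable difference at 24 per group over a stated range of SD and r. The 0.96 reliability may be cited as an upper guide to r. If baseline MoCA is a covariate, use the residual SD, SD × √(1 − r²), in place of the SD of change.
4. The Sample size section describes σ₁ and σ₂ as a pooled SD. Correct this to group-specific SDs, which is what the formula and the software option use.
5. State that a null result will be interpreted from the 95% confidence interval for the difference and not from the nominal power.

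The cost is some rewording and a small table, with no extra patients. The drawback is that one power figure becomes a conditional range.

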### Recruitment

The target population for this study consists of patients with PSCI who meet the eligibility criteria and are receiving treatment at Yueyang Hospital of Integrated Traditional Chinese and Western Medicine, Shanghai University of TCM. Recruitment will be carried out through collaboration with stroke rehabilitation units within the hospital, where neurologists and rehabilitation specialists will identify potential participants during routine clinical visits. Patients who meet the inclusion criteria will be approached by the study team and provided with detailed information about the trial. The hospital’s electronic medical records system will be used to identify stroke patients, and existing stroke patient registries will also be utilized. Recruitment posters at the clinic and website recruitment advertisements will be used.

### Assignment of interventions: allocation

#### Sequence generation

After the baseline assessment, participants will be randomly assigned to one of two groups in a 1:1 ratio using computer-generated random numbers.

#### Concealment mechanism

The allocation sequence will be concealed using sequentially numbered, opaque, sealed envelopes to ensure that the allocation remains hidden until interventions are assigned. Each envelope will contain a card indicating the group assignment (intervention or control) and will be opened sequentially only after a participant has been enrolled and baseline assessments have been completed.

The envelopes will be prepared in advance by a research assistant who is not involved in the enrollment or intervention process. The envelopes will be stored in a secure location with restricted access to prevent any potential tampering or accidental disclosure of the allocation sequence.

To further enhance the concealment, the envelopes will be identical in appearance, and the sequence number will be printed on the outside of the envelope without any indication of the group assignment inside.

#### Implementation

The allocation sequence will be generated by an independent biostatistician who is not involved in participant enrollment, intervention delivery, or outcome assessment. A computer-generated randomization program will be used, stratifying participants by age and baseline cognitive function to ensure balance between groups.

Participants will be enrolled by study clinicians who are responsible for screening and performing baseline assessments. The clinicians involved in enrollment will not have access to the allocation sequence or any information about group assignments.

After a participant has been enrolled and completed their baseline assessments, the study clinician will contact a research assistant to retrieve the next sequentially numbered, opaque, sealed envelope. The envelope will be opened in the participant’s presence, and the group assignment will be revealed. The research assistant, blinded to the allocation sequence, will assign the participant to the corresponding intervention group.

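### Randomisation is said to be stratified by age and baseline cognition, but the envelope procedure as written uses neither factor, and the primary MoCA analysis names no adjustment for them

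*Protocol article*

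**What the plan says.** Three neighbouring sections of the protocol article describe the allocation.

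- *Sequence generation*: after baseline assessment, participants are "randomly assigned to one of two groups in a 1:1 ratio using computer-generated random numbers".
- *Concealment mechanism*: "The envelopes will be prepared in advance by a research assistant" who takes no part in enrolment or treatment. For concealment, "the envelopes will be identical in appearance, and the sequence number will be printed on the outside of the envelope", with nothing to show the arm. Envelopes are "opened sequentially only after a participant has been enrolled and baseline assessments have been completed".
- *Implementation*: an independent biostatistician generates the sequence with a program, "stratifying participants by age and baseline cognitive function to ensure balance between groups". Once baseline assessment is complete, the study clinician is to "contact a research assistant to retrieve the next sequentially numbered, opaque, sealed envelope".

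No cut-points for age or cognition are given, and neither is the number of strata.

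*Statistical methods for primary and secondary outcomes* compares MoCA changes between arms by ANOVA, or by a Wilcoxon test if the data are not normal. The only covariates mentioned are lesion location and laterality, as exploratory options. *Sample size* plans 30 patients per arm and a 2-point difference in post-treatment MoCA (25.7 against 23.7).

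**The concern.** Stratification needs two things: a list for each stratum, and a dispensing step that takes the patient to the right list. The article asserts the first and describes a dispensing step without the second. A card sealed before the patient is known, and handed out in order of arrival, cannot depend on that patient's age or MoCA. Staff who follow the text would run an unstratified trial that is then reported as stratified.

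Balance on these factors matters here because eligibility is wide (age 18 to 80, any MoCA below 26 with no stated floor) and the trial is small. If the design does not balance them, the analysis should account for them, but the primary comparison as described names neither.

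**Working it through.** **1. The plan's own figures.** The inputs, from *Sample size*, are means 25.7 and 23.7 (difference 2.0), SDs 2.4 and 1.7, two-sided α 0.05, power 0.90 and dropout 20%.

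- Printed normal formula: (1.96 + 1.28)² × (2.4² + 1.7²) / 2.0² = 22.70, so 23 per arm.
- Unequal-variance t-test, the named software option: power 0.889 at 23 per arm and 0.902 at 24, so 24 per arm.
- Dropout: 24 / (1 − 0.20) = 30 per arm.

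The stated 24 and 30 reproduce. The 30 per arm and the 2-point target are used below.

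**2. Does any dispensing step use the factors?**

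| Step | Uses age or MoCA? |
|---|---|
| Program generates the sequence | Claimed |
| Envelopes filled before enrolment | No; the patient is not yet known |
| Labelling: alike, numbered | No stratum label mentioned |
| Retrieval: next number | No; order of arrival decides |
| Opening in sequence | No |

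The claim at the first step is lost by the retrieval step.

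**3. Chance imbalance in baseline MoCA.** The article gives no baseline SD, so a range of 2 to 5 is assumed. With 30 per arm, SE = SD × √(2/30) = SD × 0.258. The last column is the two-sided normal tail beyond 1/SE.

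| Assumed SD | SE of baseline difference | Chance of a gap of 1 point or more |
|---|---|---|
| 2 | 0.52 | about 0.05 |
| 4 | 1.03 | about 0.33 |
| 5 | 1.29 | about 0.44 |

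With the only MoCA SDs in the article, which are post-treatment: √((2.4² + 1.7²)/30) = √(8.65/30) = 0.54.

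**4. What a baseline gap does to the comparison.** Let D be the baseline gap and b the slope of post-treatment on baseline MoCA. A comparison of post-treatment scores shifts by b × D. A comparison of changes shifts by (b − 1) × D. For b between 0 and 1 neither is zero, though the change score removes part of the gap. A model with baseline MoCA as covariate removes it, if the relation is linear.

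**5. Balance within strata.** Four strata are assumed (two age groups by two cognition bands), with prevalences of 25% each or 40/30/20/10%. There were 10,000 simulated trials of 60 patients per setting.

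| Procedure | Chance that some stratum differs by 4 or more between arms |
|---|---|
| One series, unrestricted | 0.82 to 0.84 |
| One series, 30 cards per arm forced | 0.63 to 0.68 |
| Separate list per stratum, blocks of 4 (illustrative) | 0 |

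The balance claimed comes from separate restricted lists. One series does not give it, even when the arms are equal overall.

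**The case against.** The strongest reply is that this is a condensed article. Identical appearance is described as a safeguard against revealing the arm, and it does not rule out a numbered set for each stratum. Advance preparation is compatible with stratified envelopes. Age and MoCA are known when the envelope is fetched, and the article says outright that the program stratifies. Separate sets may therefore exist in the full protocol.

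That limits the point to the procedure as written. It does not remove it, because the article sets out retrieval step by step, and taking the next number in order reads as one series. The problem is a conflict between two statements, not a missing detail.

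A reader might go further in four ways that the documents do not support.

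- *That there is no blocking.* The article is silent on restriction, and block details are commonly left to the full protocol or withheld.
- *That the 30/30 split is not secured.* Unrestricted randomisation of 60 gives exactly 30/30 with probability 0.103, but the article does not say randomisation is unrestricted. One list with 30 cards per arm gives 30/30 with certainty, while the stratified blocks simulated above gave it in only about 43 to 44% of runs. Arm size and stratification are separate matters. Even under unrestricted randomisation, a split of 27/21 or 29/19 after dropout, with the higher-SD arm the smaller, lowers power from 0.902 to 0.883 or 0.862, so the sample size is not undermined.
- *That these are the strongest predictors of MoCA.* The article does not rank predictors.
- *That the damage is beyond repair.* An allocation cannot be redone, but chance imbalance in measured baseline factors can be adjusted for.

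**Conclusion.** The point holds for the text as published: stratification is claimed, the described envelope procedure does not deliver it, and no adjustment for the two factors is named in the primary MoCA analysis. Unstratified allocation is still valid randomisation, and nothing here suggests bias or failed concealment. The cost is possible chance imbalance and some lost precision.

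The standard error of the baseline MoCA difference is about 0.5 to 1.3 points for an assumed SD of 2 to 5, or roughly a quarter to two thirds of the 2-point target. The lower end matches the article's post-treatment SDs; the upper end rests on assumption. Not all of a baseline gap would carry into a change-score comparison. The within-stratum figures rest on four assumed strata.

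**What to change.** Reconcile *Sequence generation*, *Concealment mechanism* and *Implementation* in one of two ways.

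1. Keep the stratification. State the age and MoCA cut-points, fixed in advance. State that the biostatistician generates a separate restricted list for each age-by-MoCA stratum, that each stratum has its own labelled envelope series, and that the next envelope comes from the patient's own stratum. If this is already the practice, only the text changes.
2. Drop the stratification claim and describe the single series as it is used.

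In either case, specify baseline MoCA and age as covariates in the primary between-group model. Both are collected before allocation, so this needs no new data. It recovers precision whichever procedure was used.

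The cost is a paragraph of protocol text and, for the first option, re-cut lists and relabelled envelopes before the next randomisation. Small blocks would make allocation slightly more predictable at a single site with unblinded therapists. Varying the block sizes and keeping them from site staff limits this.

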In the control group, participants will receive single-target tDCS, targeting only the DLPFC. The parameters for this group will be identical to those for the intervention group, except that the AG will not be stimulated. Instead, sham stimulation will be applied to the AG, simulating the sensation of tDCS without delivering an active current. Set the SHAM switch to ON, enabling the sham mode. During this mode, the current ramps up to the set intensity over a period of 30 s at the beginning of the session and ramps down in 30 s. No stimulation is delivered during the interim period. This ramp-up and ramp-down process is repeated at the end of the session to mimic the sensory perception of active stimulation without inducing neuromodulatory effects. This approach will help maintain blinding between the groups.

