### Assignment of interventions: blinding

#### Who will be blinded

Participants will be blinded to their group assignment (intervention or control). They will not know whether they are receiving active dual-target a-tDCS or sham stimulation, ensuring that their expectations do not influence the outcomes.

The therapists administering the tDCS will not be blinded to the group assignments. They will know whether they are providing active or sham stimulation due to the nature of the intervention.

Outcome assessments will be conducted by clinicians who are blinded to the participants’ group assignments. Each participant will be identified by a unique study number, and the outcome data will be recorded without revealing the group allocation.

Data analysis will be performed by an independent data analyst who will be blinded to the group assignments. The analyst will work with de-identified data, ensuring that the analysis remains unbiased.

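### The allocation envelope is opened in front of the participant and the arm revealed, which contradicts the participant blinding the trial claims

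*Protocol article*

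**What the plan says.** The allocation procedure is spread over two sections of the protocol article. Under Concealment mechanism, the sequentially numbered, opaque, sealed envelopes are described as follows: "Each envelope will contain a card indicating the group assignment (intervention or control". Under Implementation, once baseline is complete the study clinician asks a research assistant for the next envelope, and then: "The envelope will be opened in the participant’s presence, and the group assignment will be revealed".

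The blinding statements are elsewhere. Trial design labels the study: "This study is a single-center, participant-blinded, parallel-group, randomized controlled trial with a 1:1 allocation ratio". It adds: "Participants will be blinded to the intervention they receive". Who will be blinded repeats the commitment, "Participants will be blinded to their group assignment (intervention or control", and gives its purpose as "ensuring that their expectations do not influence the outcomes".

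In the control arm, Intervention description says that "sham stimulation will be applied to the AG, simulating the sensation of tDCS without delivering an active current", and gives the reason: "This approach will help maintain blinding between the groups". The section on unblinding reserves it for cases where a participant's safety requires it. Implementation also says that enrolling clinicians have no information about group assignments.

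**The concern.** The information that participants must not have is the information on the card. A procedure that opens the card in front of them and reveals the assignment puts it within their reach before any stimulation is given.

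Three things are at stake:

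- **The sham.** Both arms receive active DLPFC stimulation and differ only in whether the AG electrode delivers current. The sham at the AG is there to hide that difference. If the arm has already been disclosed, the sham no longer hides it.
- **The outcomes.** The primary outcome (MoCA) and the digit span and Trail Making tests are performance tests, on which effort and expectation can act. The article itself relies on participant blinding to rule this out. There is no dual-sham arm, so the contrast between the two arms is the only efficacy comparison. An expectation difference between arms would be confounded with the stimulation effect, and no analysis of the planned data could separate the two.
- **The label.** A trial run this way could not properly be reported as participant-blinded.

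**Working it through.** No calculation decides this point. The check is whether the stated procedures can all be followed at once.

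**Step 1. Statements side by side**

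| Section | What it requires |
|---|---|
| Concealment mechanism | The card states the group: intervention or control |
| Implementation | The envelope is opened with the participant present and the assignment revealed |
| Trial design | The participant does not know the intervention received |
| Who will be blinded | The participant does not know the group, so that expectations play no part |
| Intervention description | AG sham in controls preserves the blind |
| Procedure for unblinding | Unblinding only for safety reasons |
| Implementation (enrolling staff) | Enrolling clinicians hold no information about assignments |

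The first two rows together put the group label in front of the participant. The next four require that the participant never has it, outside a safety event.

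**Step 2. Is there a safeguard?** The article does not say that the card is coded, that it is shown only to the operator, or that it is kept from the participant. The only description of its content is the group name.

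**Step 3. Two readings of the opening step**

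- *Revealed to everyone present, including the participant.* This is the natural reading. Participant blinding is then lost at allocation.
- *Revealed to staff only, with the participant present.* The blind could survive, but only through precautions that the article does not state.

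Under the first reading the article contradicts itself. Under the second, it describes a step that puts the blind at risk and leaves its protection to chance.

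**Step 4. When and how many.** The envelope is opened after enrolment and baseline, hence before session 1. The step applies to every randomised participant. The planned number follows from the Sample size section: 24 per group with 20% dropout gives 24 / (1 − 0.20) = 30 per group, and 2 × 30 = 60. So up to 60 of 60 are exposed. The 24 itself reproduces: the unequal-variance t-test that the section names (difference 25.7 − 23.7 = 2.0, SDs 2.4 and 1.7, two-sided 0.05) gives power 0.889 at 23 per group and 0.902 at 24. The sample size is not affected by this point.

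**Step 5. Who else is in the room.** The study clinician calls for the envelope. The section does not say whether that clinician stays for the opening, although enrolling clinicians are to know nothing of assignments. This is left open, not shown to be breached.

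**The case against.** The best defence is that the sentence in Implementation is in the passive and names no recipient. Who will be blinded says plainly that participants will not know what they receive, so the intention may have been to open the envelope with the participant present and show the card only to staff. The ambiguity is real and it limits how strongly the point can be put. It does not remove the point, because the natural reading includes the participant and the other reading comes with no safeguard.

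A second defence is that an article condenses a fuller protocol. That would excuse a missing detail. Here the article states a specific step that conflicts with its own blinding statements.

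A reader might also infer four stronger things, which the article does not support:

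- **That the blind is certain to be destroyed.** This depends on the participant seeing or hearing the card, which is likely on the wording but not stated.
- **That assessor blinding is broken too.** The outcome assessors are described as clinicians blinded to assignment. Nothing says that they are the enrolling clinicians or that they attend the opening. An informed participant could tell an assessor, but that is a risk, not a documented breach.
- **That participants are told dual-target is expected to work better.** The Informed consent section repeats the trial's hypothesis, but it does not say that this is put to participants, and the consent form is not available for review.
- **That the bias can be put in MoCA points.** The article offers no basis for any figure, nor for asserting a direction as fact.

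**Conclusion.** The point holds as a contradiction between the allocation procedure and the trial's blinding. The opening step in Implementation cannot be carried out, on its natural reading, together with participant blinding under Trial design and Who will be blinded, the purpose of the AG sham, and safety-only unblinding.

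The exposure is up to all 60 participants, before session 1. This assumes that revealing the assignment in the participant's presence means that the participant learns it. If only staff were meant, the fault is an unprotected step and not a certain disclosure, and the text still needs correcting. The size of any resulting bias cannot be derived from the document. What can be said is that it would be inseparable from the treatment effect on performance-based outcomes and could not be undone once participants know their arm. It should therefore be fixed before participants are allocated under this text. The presence of the enrolling clinician at the opening is a secondary ambiguity to settle in the same amendment.

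**What to change.** Amend the Implementation section to state that:

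1. the tDCS operator, who is already unblinded, opens the envelope out of sight and hearing of the participant, the enrolling clinician and all outcome assessors;
2. the assignment is not disclosed to the participant;
3. anyone who has seen the card does not perform outcome assessments.

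It is better to name the operator than a research assistant. Concealment mechanism has one assistant preparing the envelopes, Implementation has one described as blinded to the sequence, and the article does not say whether they are the same person. The sentence that has the assistant assign the participant should be brought into line.

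The card need not be coded, because the operator is permitted to know the arm. Sequential numbering and opening only after baseline stay as they are, so allocation concealment is not weakened.

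The cost is a short protocol amendment with ethics approval and a change in where, and by whom, the envelope is opened. No extra staff are needed, and the sample size and analysis are unchanged.
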